**Affect**				
How do you feel at the moment? nervous (Item 1), alert (Item 2), upset (Item 3), scared (Item 4), inspired (Item 5), enthusiastic (Item 6), afraid (Item 7), determined (Item 8), irritable (Item 9), excited (Item 10), stressed (Item 11), sad (Item 12) *1 (very slightly or not at all) – 2 (a little) – 3 (moderately) – 4 (quite a bit) – 5 (extremely)*		x	x	-

#### Measures for the intensive-longitudinal phase: ecological momentary assessment

PA is measured objectively by accelerometer and self-report, sedentary behavior by accelerometer only. Back health and psychological determinants of LTPA will be assessed, including items adapted from previous studies or from longer questionnaires and adapted for EMA purposes.

##### Self-report EMA measures

Participants will be asked to complete self-report EMA measures at a pre-specified time each day. Measures taken at each data collection point in the morning will include *intention*,* self-efficacy* [43, 44], *planning* [48], and *affect* [58, 59]. Measures taken at each afternoon data collection occasion will include *social support* [63, 64], *time pressure*, and *job control*, adapted from [55]. Measures taken at each data collection point in the evening will include LTPA, *plan enactment*, adapted from [65], *habit strength* [50], *low back health*,* LBP intensity* and *disability* [39], *working hours*, *breaks*, and *recovery experience* [66] (Table 2). Each evening, participants are asked how typical their day was and whether anything unusual happened that could have affected their LTPA or accelerometer. In terms of LTPA, participants report whether they did any activity, and if so, what activity they did, when they did it and how long it lasted. This information is used to validate the accelerometer data and to determine the type of LTPA for descriptive purposes (Table 2). At the first follow-up of the LL phase, we also assess reactivity to the IL phase assessment (Table 1).

To obtain an objective measure of LTPA, we use the self-reported work time as a marker for the accelerometry data. By combining these two sources of data, we will be able to distinguish between accelerometer data during work and during non-work time (i.e., leisure-time). The same procedure will be used to obtain a measure for sedentary time during work and leisure-time.

##### Objective EMA measures

For accelerometry we use the Move4 [67] which is a sensor based on triaxial acceleration, gyroscope, barometric air pressure, and temperature. It measures acceleration with a measurement range of ± 16 g and an output rate of 64 Hz, for further specifications, see [68]. Raw data is downloaded from the accelerometers via the SensorManager (movisens GmbH). The accelerometer determines the non-wear time in 30 s intervals [69]. Self-reported data on leisure-/work time information (Table 2, ambulatory assessment, e.g., 9:30 am- 4:30 pm) is checked for plausibility, corrected, and combined with the accelerometer signal by an Octave (GNU Octave, version 7.1.0) script provided by movisens. This enriched raw data is run through the DataAnalyzer software (movisens GmbH, version 1.16.3) to obtain 60 s outputs. Following proprietary algorithms [70], the DataAnalyzer produces physical activity intensity and energy expenditure results based on activity-related regression models, fed by participant characteristics (gender, age, weight, height). Results contain minute-by-minute METs (1 MET equals the energy expenditure at rest), steps, and energy expenditure in calories. MVPA outside of working hours is based on MET-values > 3 MET. Light physical activity is categorized for > 1.5–3 MET. By combination with self-reported work time, LTPA is available on a minute-by-minute basis and will be the main outcome measure of the EMA study. Daily wear time is calculated by subtracting non-wear time from the daily recording time (e.g., 24 h). Following Troiano, Berrigan [71], days with ≥ 10 h of wear time will be considered valid. Participants with ≥ 3 valid days will be included in the data analysis [72]. We will check and potentially control for the initial elevation bias [73].

Sedentary behavior is operationally defined as any behavior in a sitting, reclining, or lying position with ≤ 1.5 MET, excluding sleep [74, 75]. Minute-by-minute sedentary behavior during leisure-time and at work are used as a secondary outcome. To maximise the amount of data available for PA, participants will be reminded to charge their Move4 device every 5 days. If participants agree, we will also contact them via their study smartphone 1 week into the study to see if there are any technical problems with any of the devices.

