## Methods

### Study design and procedures

This study is a prospective longitudinal observational cohort study, taking place over a period of 2 months, with an intensive-longitudinal ecological momentary assessment (EMA) phase (Fig. 2). Participants provide self-report questionnaire data at baseline (Time 0, T0), with subsequent follow-up questionnaires (Time 1–3, long-longitudinal design; LL) collected electronically via an online survey platform (Unipark, Tivian XI GmbH, Cologne, Germany) from a study tablet or computer on-site (T0) or on a personal device at home (e.g., computer, tablet, smartphone; Time 1–3). The study will involve a 1.5 h baseline session at MSB Medical School Berlin or Charité Universitätsmedizin Berlin or participants’ workplace, during which demographics, PA and sedentary behavior, physical and mental health, as well as theory-driven psychological variables will be assessed. During the baseline session, participants will also undergo objective measurements of their back posture and mobility. Participants will then receive training in the time-sampling protocol, the handling of their Android study phone (Nokia 6.3) with the movisensXS app (movisens GmbH) and accelerometer (Move4, movisens GmbH). Starting at T0, participants will wear an accelerometer and will be asked to complete three daily questionnaires on their study smartphone for the following 14 days (intensive-longitudinal design; IL; Fig. 2). Participants will receive three alarm-triggered daily life surveys via the movisensXS app at 8 am (“morning questionnaire”), 3 pm (“after work questionnaire”), and 9 pm (“evening questionnaire”). Participants can delay responding until 3 h after the time prompt, and reminders are sent every 20 min during this window. After this time, the questionnaires will no longer be available to prevent backfilling. Daily life assessments take 2 to 6 min each to complete, resulting in a total of 1.5–4.5 h to complete the diaries over the entire IL phase. Accelerometers will be worn on a belt clip placed at the right hip (i.e., the right anterior iliac crest) and do not require any attention from participants. Participants are instructed to wear the accelerometer during waking hours for 2 weeks and to recharge the battery at least every 5 days. Throughout the study, participants are encouraged to carry out their usual daily activities. The device has no monitor and does not provide activity feedback. Within 2 weeks of the end of the intensive longitudinal phase (1–15 days), participants return their materials (i.e., study phone and accelerometer) and complete a 30-minute exit session to receive feedback on their back posture and mobility. Each participant will be compensated with a minimum of €40 for this study.

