**Job demands and resources**				
Did you work today? *1 (yes) − 2 (no); [If 1 (yes)]* From when until when did you work today? *From (time*, e.g.,* 9:00 am) ___ Until (time*, e.g.,* 4:00 pm) ___;* Have you taken at least one break of at least 15 min today? *1 (yes) − 2 (no)*; *[If 1 (yes)]* How long was your break? If you took more than one break, think of the longest. *From (time*, e.g.,* 12:00 pm) ___* *Until (time*, e.g.,* 1:00 pm) ___*	Working hours and breaks	-	-	x
Are you still working? *1 (yes) − 2 (no) – 0 (I did not work today)*; *[only for 1 (yes) and 2 (no)]* Are you working from home today? *1 (yes) − 2 (no)*	Work place	-	x	-
How often have you been under time pressure for professional reasons today? *1 (very seldom/never) – 5 (very often/always)*	Time pressure	-	x	-
Were you able to choose the way you did your work today? *1 (very seldom/never) – 5 (very often/always)*	Job control	-	x	-
This evening I didn’t think about my work at all. (Item 1)/ This evening I used the time to relax. (Item 2)/ This evening I did things that challenged me. (Item 3)/ This evening I felt I could decide for myself what to do. (Item 4) *1 (does not apply at all) − 5 (applies completely)*	Recovery experience	-	-	x

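### The 10 h whole-day wear rule does not secure enough leisure-time wear for the accelerometer LTPA outcome, which counts only non-work minutes

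*Protocol article*

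**What the plan says.** Under Objective EMA measures, wear time is whole-day recording time (24 h is the example) minus detected non-wear, and "days with ≥ 10 h of wear time will be considered valid". At person level, "Participants with ≥ 3 valid days will be included in the data analysis". Neither rule refers to work or leisure.

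The outcome does refer to them. The same section states: "By combination with self-reported work time, LTPA is available on a minute-by-minute basis and will be the main outcome measure of the EMA study". It also lists minute-level sedentary behaviour, split into leisure and work, as a secondary outcome.

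The split depends on self-report. Under Self-report EMA measures: "we use the self-reported work time as a marker for the accelerometry data". Table 2 asks for the clock times ("From when until when did you work today") in the evening questionnaire only. Under Study design and procedures, each questionnaire stays open for 3 h: "After this time, the questionnaires will no longer be available to prevent backfilling". A work-time report "is checked for plausibility, corrected, and combined with the accelerometer signal", but the article states no rule for a day without a report.

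**The concern.** A validity rule should show that the period in which the outcome occurs was observed. Ten hours of total wear does this for whole-day activity. For an outcome confined to leisure, the hours worn at work count towards validity and contribute nothing to the outcome.

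If the belt comes off some time after work, the day remains valid and its LTPA minutes come from only part of the leisure period. The leisure wear that the rule requires falls hour for hour as the workday lengthens. The within-person hypotheses predict less LTPA on days with higher job demands. If such days are also longer, and evening wear is incomplete, the shortfall in recorded minutes goes in the hypothesised direction.

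**Working it through.** The article does not derive the 10 h threshold, so there is no figure of the plan to reproduce. The check asks how much leisure wear the rule guarantees.

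**Inputs**
- Threshold: 10 h of total wear (Objective EMA measures).
- Work span W: the article's example, 9:30 am to 4:30 pm, gives 16.5 − 9.5 = 7 h. Other values of W are for illustration.
- Wear instruction: waking hours (Study design and procedures). Their length is not given; 16 h is assumed, with a range of 15 to 17 h.
- The device is assumed to be worn throughout work.

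**Formulas**
- Least leisure wear on a valid day = max(0, 10 − W).
- Least share of leisure observed = max(0, 10 − W) / (waking hours − W).

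| W (h) | Least leisure wear (h) | Leisure available at 16 h awake (h) | Least share | Range for 15–17 h awake |
|---|---|---|---|---|
| 0 (free day) | 10 | 16 | 63% | 59–67% |
| 4 | 6 | 12 | 50% | 46–55% |
| 7 | 3 | 9 | 33% | 30–38% |
| 8 | 2 | 8 | 25% | 22–29% |
| 9 | 1 | 7 | 14% | 12.5–17% |
| 10 | 0 | 6 | 0% | 0% |

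So a 7 to 8 h workday can be valid with about two thirds to three quarters of leisure unobserved, while a free day cannot.

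**Why total wear is not a sufficient covariate.** Take two days with exactly 10 h of wear, one with 7 h of work and one with 10 h. Total wear is equal, but leisure wear is 3 h and 0 h.

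**Size of the bias, all inputs assumed.** True leisure activity is 40 min/day, spread evenly over leisure. A share q of days has 25% of leisure observed, and raw minutes are analysed. The mean falls by 40 × q × (1 − 0.25):
- q = 10%: 3 min/day
- q = 30%: 9 min/day

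**Group difference, same assumptions, SD 30 min.** False d = 40 × 0.75 × (q2 − q1) / 30:
- 10% in both groups: 0
- 10% and 20%: 0.10
- 10% and 30%: 0.20

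**Days without a work interval.** With assumed evening response of 90%, 80% or 70%, the expected number among 14 days is 14 × 0.10 = 1.4, 14 × 0.20 = 2.8 or 14 × 0.30 = 4.2. Such days can meet the wear rule and still have no basis for separating work from leisure.

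**The case against.** The case on the other side has real force.

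- **Ten hours is a floor.** Participants are told to wear the device in all waking hours, and eligibility starts at 20 working hours per week, so shorter workdays and free days will be among the 14. A reader might infer that valid days commonly hold almost no leisure data. The documents do not support that: the guaranteed minimum approaches zero only for work spans of about 9 to 10 h or more, and no wear data are given.
- **There are partial safeguards.** Each evening, participants report the start, type and duration of LTPA and anything unusual affecting their activity or the accelerometer. These items can reveal a belt taken off for sport. They sit in the same evening questionnaire as the work times, however, so they are lost with it, and no stated rule lets them change a day's validity.
- **A missing work interval.** A reader might infer that such days count as low-LTPA days, or that physiotherapists' manual work is then counted as leisure. The article obtains LTPA only by combining both sources, so without the interval the outcome is undefined. Nothing says that the whole day is treated as leisure.
- **Group differences.** A reader might infer that the two work groups are affected unequally. The documents say nothing about differences in wear, evening response or workday length. With equal shares the false difference is zero.
- **An analysis plan may add detail.** It may, for example, set a leisure-wear covariate. But this article already fixes which days and participants enter, and that stated rule does not fit the outcome.

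**Conclusion.** The point holds as a mismatch between a stated rule and the outcome it serves. A valid day guarantees neither adequate leisure wear nor a known work interval. With the device worn throughout work, the guaranteed leisure wear is 3 h at the article's 7 h example, 2 h at 8 h and none from 10 h. The shares (33%, 25%, 0%) rest on the assumed 16 waking hours.

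Under-recording follows only where leisure wear is in fact incomplete and raw minutes are used. How often that happens cannot be known from the documents, so the 3 to 9 min/day is an illustration and not an estimate. A link with job demands is plausible because tolerance grows with workday length, but it also needs demands to track long days. A difference between work groups is possible and undocumented.

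The scope is accelerometer LTPA and leisure sedentary time in the EMA multilevel models and the N-of-1 studies. A reader might extend it to the between-group t-tests. Those belong to the long-longitudinal phase, where LTPA comes from the IPAQ leisure items, and they are untouched.

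**What to change.** 1. Keep the 10 h rule for total physical activity.
2. For LTPA and leisure sedentary time, pre-specify a minimum of non-work wear, include daily non-work wear time as a covariate, or do both. Adjustment for total wear is not enough.
3. Treat days without a reported work interval as missing for these two outcomes. A free day reported in the evening questionnaire counts as known. The afternoon item cannot replace it: it is prompted at 3 pm, gives no clock times and cannot rule out later work.
4. Apply the three-valid-days rule to the days that remain.
5. Report a sensitivity analysis over several leisure-wear thresholds. The documents give no basis for deriving a single value.

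The cost is reprocessing of existing minute-level data and the loss of some days and possibly some participants. Two choices need a sentence in the plan. A minimum in hours is stricter on long workdays than a proportion, while a proportion needs an assumption about waking time. The covariate also absorbs the genuine shortening of leisure on long workdays, so its coefficients should be read as effects at a given amount of observed leisure time.

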#### Measures for the intensive-longitudinal phase N-of-1: ecological momentary assessment

The subgroup of *N*-of-1 participants receive the same self-report and objective EMA measures as described for the IL phase of the main study. An additional feature is the option to capture any written or photo notes at any point in time in the app. If participants like to leave a note, they will be able to select a questionnaire in the app and answer “What was relevant for your physical activity during leisure (just now)?” by text or “Maybe a picture says more than 1000 words: show us, alternatively, what was relevant (just now) for your physical activity in your leisure-time” by taking a photo.

*N*-of-1 participants will also participate in a data-prompted, semi-structured qualitative interview [26, 27] at the end of the study. The interview questions relate to experiences with the research questions and measurement responsiveness and are conducted by a research assistant experienced in interviewing. Interviews will be audio-recorded using a digital recorder, transcribed using the program f4transkript (audiotranskription dr.dresing & pehl GmbH, Marburg, Germany) and anonymized. The program f4analyze (dr. dresing & pehl GmbH, Marburg, Germany) will be used for coding by two researchers.

### Power analysis

An a priori power analysis with G*Power [76] was performed for the primary between-subject research questions on the difference between two work contexts for LTPA. At a significance level of 5%, a power of 95%, a medium effect of d = 0.5, and equal sample sizes we would require a sample size of 210 participants. Accounting for a potential dropout of 20%, this increases to a sample size of 252 participants.

A priori power analyses for examining the link between LTPA and behavior-related outcomes (i.e., low back pain) at a significance level of 5% and 95% power, result in different sample sizes, depending on the effect size of the relationship that we expect between the specific behavior-related outcome and LTPA. It ranges from an expected small effect size, resulting in 115 participants, to a medium effect size resulting in 38 participants.

A path analytic approach to test our assumptions on the links between theory-based, psychological variables and LTPA (Fig. 1) necessitates a minimum of 210 participants [77].

Regarding a priori power analyses for multilevel models this study referred to heuristics presented in Arend and Schäfer [78], who had run Monte-Carlo simulations with a minimum of 80% power for different conditions on the smallest necessary sample size. At a significance level of 5%, a minimum of 80% power, a medium intraclass coefficient, and a minimum of *n*_Level−1_ = 14 days of assessment (i.e., number of repeated measurements within persons), small correlations for the primary outcome (LTPA) with a predictor (Level-1/day-level, e.g., intention) [79] would require a minimal Level-2 sample size of *N* = 150 (i.e., number of required individuals). For medium correlations of the outcome with a predictor (Level-2/person-level, e.g., work context), a significance level of 5%, a minimum of 80% power, a medium intraclass coefficient (ICC = 0.50) and a minimum of *n*_Level−1_ = 14 days of assessment, a minimal sample size of *N* = 100 would be required. Considering a potential dropout of 20% for the larger sample size, this estimation increases to *N* = 180.

For observational *N*-of-1 studies, there is currently no gold standard for power analyses, especially as any power is person-specific depending on e.g., individual effect size or number of observations. However, it is generally recommended to use a minimum of 50 observations in order to achieve statistically relevant results [25, 80] and good estimates [81]. To account for the potential missing data of 20%, we planned for a total of 68 days in the study.

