**Methods:**

The proposed study is a longitudinal observational study taking place over 2 months with an intensive-longitudinal ecological momentary assessment (EMA) phase. A sample of 252 adults will be recruited from two working populations, sedentary workers, and manually working physiotherapists. At baseline, participants complete a self-report questionnaire and undergo an objective measurement of their back posture and mobility. At 2, 4, and 8 weeks after baseline, participants fill in the follow-up questionnaires. Starting at baseline, participants will also wear an accelerometer and will complete three daily questionnaires for the following 14 days. In addition to the main study, a sub-sample of 8 observational *N*-of-1 studies will have an extended EMA phase of 68 days and a data-driven exit interview. The primary outcome is moderate-to-vigorous LTPA. Data will be analyzed using regression and multi-level models. For the *N*-of-1 studies, a mixed-methods approach will be used including dynamic regressions.

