
**Fig. 2 Fig2:**
[figure not shown]
Study design

A subgroup of interested participants will participate in an observational *N*-of-1 time-series approach [25] over 2.5 months with prospective IL assessments only. Baseline measurements are the same as in the main study including a self-report questionnaire and an objective back posture and mobility measurement, followed by 67 more days of EMA assessments. *N*-of-1 participants will not receive follow-up questionnaires. Within 2 weeks of the end of the IL phase (day 1–68), participants will return their materials (i.e., study phone and accelerometer) and complete a 60-minute exit session to receive feedback on their back and to take part in a data-prompted, qualitative interview [26, 27]. The university’s ethics committee at MSB Medical School Berlin granted approval on 29/03/2021 (approval number MSB-2021/62) for the study, including data management and data protection procedures. Written informed consent will be obtained from each participant prior to enrolment. The pre-registration in the publicly available German Clinical Trials Register (DRKS-ID: DRKS00025296) took place on 28/06/2021. The actual study start date was 22/07/2021 and recruitment continued until the end of the funding period (30/06/2024). All data will be stored on a secure server at the two institutions. Primary data, such as participant-reported outcomes, will be pseudonymized.

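### The 20% dropout allowance multiplies by 1.2 instead of dividing by 0.8, so the target of 252 covers only 16.7% dropout

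*Protocol article*

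**What the plan says.** All the figures are in the Power analysis section of the protocol article.

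- For the primary between-person question, the difference in LTPA between two work contexts, the inputs are "At a significance level of 5%, a power of 95%, a medium effect of d = 0.5" and equal groups. They give 210 participants.
- The allowance for loss follows directly: "Accounting for a potential dropout of 20%, this increases to a sample size of 252 participants".
- The path analysis of the theoretical model "necessitates a minimum of 210 participants". No separate dropout allowance is given for it.
- For the multilevel models, the larger of two minimum numbers of persons is 150. The text continues: "Considering a potential dropout of 20% for the larger sample size, this estimation increases to" 180.

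The Methods part of the Abstract carries the result forward as the recruitment target: "A sample of 252 adults will be recruited from two working populations".

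**The concern.** A dropout allowance should ensure that the required number remains after the assumed loss. Dropout is a share of those enrolled, so the required number has to be divided by the proportion expected to stay. Multiplying by one plus the dropout rate gives too few. Both inflated figures in this section are exact multiples of 1.2, which points to this slip.

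The figure of 252 is the headline target of the study. The article presents it as protecting 95% power against a 20% loss, and the same 252 has to supply the path model, whose stated minimum is also 210. If the allowance is wrong, the article claims a margin that its own numbers do not give.

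**Working it through.** **Inputs, all from the Power analysis section:** significance level 5%, power 95%, d = 0.5, equal groups, dropout 20%; path-model minimum 210; multilevel minimum 150, inflated to 180. The test is a two-sample t-test (Hypothesis tests for long-longitudinal phase). Sidedness is not stated.

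**1. Reproduce 210.** A two-sided two-sample t-test (noncentral t) with d = 0.5, alpha 0.05 and power 0.95 needs 104.93 per group, so 105 per group and 210 in total. Power at 210 is 0.9501. A one-sided test would need 87.26 per group, so 88 per group and 176 in total. Only the two-sided test reproduces 210, and it is assumed from here on.

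**2. Reproduce 252.**
- N × (1 + 0.20) = 210 × 1.2 = 252, an exact match.
- N / (1 − 0.20) = 210 / 0.8 = 262.5, so 263, or 264 (2 × 132) for equal groups. This is 11 to 12 more than 252, too large a gap for rounding.

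**3. What 252 gives.**
- Remaining after 20% dropout: 252 × 0.8 = 201.6, about 201 to 202.
- Shortfall against 210: 210 − 201.6 = 8.4, so 8 to 9 people.
- Dropout that 252 can absorb: 1 − 210/252 = 16.7%.

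**4. Power of the group comparison (two-sided, d = 0.5, equal split).**

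| Total analysed | Power |
|---|---|
| 210 | 0.950 |
| 202 | 0.942 |
| 201 | 0.941 |

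The loss is just under one percentage point.

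**5. Path model.** About 201 remain against the stated minimum of 210. This shortfall applies only if the model is restricted to those who do not drop out.

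**6. Multilevel models.**
- 150 × 1.2 = 180 matches the article, but 180 × 0.8 = 144, which is below 150.
- The correct figure is 150 / 0.8 = 187.5, so 188.
- The study plans for 252, not 180. About 201 remain after 20% dropout, which is 51 above 150.

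**7. Comparison with the N-of-1 allowance.** The minimum there is 50 observations and the plan is 68 days. With 20% missing, 68 × 0.8 = 54.4, which is above 50. That allowance protects its minimum; the two above do not.

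**The case against.** The strongest reply is that the slip changes nothing of substance. Power of 94% instead of 95% leaves the group comparison well powered for d = 0.5, and no design decision turns on the difference. That stands, and it is why the point is minor.

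Several stronger readings are tempting, and the documents do not support them.

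- **The path model will fall short of its minimum.** A reader might infer this from 201 against 210. However, Table 1 shows that the questionnaire measure of LTPA and all the theory-driven psychological variables are collected at baseline, and the analysis section does not tie the path model to a follow-up visit or to completers. People who drop out later may still be analysable. The shortfall is therefore conditional.
- **The multilevel minimum fails.** A reader might infer this from 144 against 150. That describes a sample of 180, which nobody planned to recruit.
- **The N-of-1 participants reduce the 252 further.** The Abstract describes them as additional to the main study, Sample and recruitment offers that design as an alternative to it, and they are analysed separately. The text places them outside the 252.
- **There was no real target.** The article says that "recruitment continued until the end of the funding period (30/06/2024"), but it also states 252 as the planned sample. It does not give the number achieved, so a shortfall in recruitment cannot be inferred.

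One could also read 20% as a share of the required 210, that is 42 people, which would make 252 correct. The article does not define it so, and dropout ordinarily means a share of those enrolled.

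**Conclusion.** The arithmetic is wrong as written: 252 allows for 16.7% dropout, not 20%, and 180 should be 188. At the plan's own 20%, about 201 of 252 remain. Power for d = 0.5 is then about 94% instead of 95%, and the path model is 8 to 9 people below its stated 210 if dropouts cannot be analysed. The multilevel minimum of 150 is met.

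The result rests on three assumptions: a two-sided test, which is the only version that reproduces 210; dropout counted as a share of those enrolled; and, for the power figure, that those who drop out contribute nothing to the group comparison. If some of them are analysable from baseline data, the loss is smaller. The error itself is certain, its consequence is slight, and the severity is minor.

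**What to change.** Keep 252 as the target that was used, since replacing it with 264 would misreport the plan, and correct the statement around it. Suggested wording:

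> The target of 252 allows for 16.7% dropout from the required 210. With 20% dropout, about 201 participants remain, giving about 94% power for d = 0.5. This is below the path-analysis minimum of 210 if participants who drop out cannot be analysed. Full allowance for 20% dropout would have needed 263 participants (264 for equal groups).

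In the multilevel paragraph, change 180 to 188 and add that the planned 252 still leaves about 201 after 20% dropout, above the minimum of 150.

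The cost is a few sentences and slightly less favourable figures. The design, the analyses and recruitment stay as they are.
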